## Abstract

**Background:**

Alcohol and other substance use disorders usually begin with substance use in adolescence. Pediatric primary care offices, where most adolescents receive health care, are a promising venue for early identification of substance use and for brief intervention to prevent associated problems and the development of substance use disorder.

**Objective:**

This study tests the effects of a computer-facilitated screening and brief intervention (cSBI) system (the *CRAFFT [Car, Relax, Alone, Forget, Family/Friends, Trouble] Interactive System* [CRAFFT-IS]) on heavy episodic drinking, riding with a driver who is substance impaired, or driving while substance impaired among adolescents aged 14 to 17 years presenting for a well visit at pediatric primary care practices.

**Methods:**

We are conducting a cluster randomized controlled trial of the CRAFFT-IS versus usual care and recruiting up to 40 primary care clinicians at up to 20 pediatric primary care practices within the American Academy of Pediatrics (AAP) Pediatric Research in Office Settings network. Clinicians are randomized 1:1 within each practice to implement the CRAFFT-IS or usual care with a target sample size of 1300 adolescent patients aged 14 to 17 years. At study start, intervention clinicians complete web-based modules, trainer-led live sessions, and mock sessions to establish baseline competency with intervention counseling. Adolescents receive mailed recruitment materials that invite adolescents to complete an eligibility survey. Eligible and interested adolescents provide informed assent (parental permission requirement has been waived). Before their visit, enrolled adolescents seeing intervention clinicians complete a self-administered web-based CRAFFT screening questionnaire and view brief psychoeducational content illustrating substance use–associated health risks. During the visit, intervention clinicians access a computerized summary of the patient’s screening results and a tailored counseling script to deliver a motivational interviewing–based brief intervention. All participants complete previsit, postvisit, and 12-month follow-up study assessments. Primary outcomes include past 90-day heavy episodic drinking and riding with a driver who is substance impaired at 3-, 6-, 9-, and 12-month follow-ups. Multiple logistic regression modeling with generalized estimating equations and mixed effects modeling will be used in outcomes analyses. Exploratory aims include examining other substance use outcomes (eg, cannabis and nicotine vaping), potential mediators of intervention effect (eg, self-efficacy not to drink), and effect moderation by baseline risk level and sociodemographic characteristics.

**Results:**

The AAP Institutional Review Board approved this study. The first practice and clinicians were enrolled in August 2022; as of July 2023, a total of 6 practices (23 clinicians) had enrolled. Recruitment is expected to continue until late 2024 or early 2025. Data collection will be completed in 2025 or 2026.

**Conclusions:**

Findings from this study will inform the promotion of high-quality screening and brief intervention efforts in pediatric primary care with the aim of reducing alcohol-related morbidity and mortality during adolescence and beyond.

**Trial Registration:**

ClinicalTrials.gov NCT04450966; https://www.clinicaltrials.gov/study/NCT04450966

**International Registered Report Identifier (IRRID):**

DERR1-10.2196/55039

## Introduction

### Background and Rationale

Alcohol and other drugs are a major contributor to morbidity and mortality each year [1]. Most substance use disorders (SUDs) have a pediatric origin, and substance use remains among the most prevalent of adolescent risk behaviors [2-4]. In addition, motor vehicle crashes remain a leading cause of death among adolescents, and alcohol- or drug-impaired driving and riding with a driver who is substance impaired play a major role [5].

Pediatric primary care offices, where the majority of adolescents receive health care [6], are a promising venue for early identification of problematic substance use among adolescents and for brief intervention to prevent further problems. A substantial and increasing proportion of adolescents see a primary care clinician yearly [7] and have trusting, longitudinal relationships with their clinicians [8]. Primary care visits are opportunities for private conversations that support adolescents’ autonomy and confidentiality while placing topics such as substance use in a nonpejorative health risk context.

The American Academy of Pediatrics (AAP) recommends alcohol, tobacco, and other drug use annual screening as part of routine care starting at age 11 years [9,10]. However, a national survey found that only approximately half of adolescents who had a past-year visit with a physician reported being asked about alcohol use [11,12]. Even when substance use screenings are performed, they can be of low quality if clinicians do not use a structured, validated screening tool or if they ask questions while caregivers are present [13,14]. Screenings also seldom include questions about substance-impaired driving or riding with a driver who is substance impaired [15]. Pediatric primary care clinicians also face barriers to brief intervention based on screen responses, including insufficient time during the appointment, a lack of familiarity with validated screening tools, and a lack of experience with managing care for patients who screen positive [16-18].

To overcome these barriers, digital technology can be applied to support consistent, effective screening and tailored intervention for adolescent substance use using evidence-based tools and approaches [19,20]. Clinicians may prefer to use technological tools such as tablet computers for previsit screening and electronic medical record–embedded decision support to enable brief intervention delivery [21]. Accordingly, we designed the CRAFFT (Car, Relax, Alone, Forget, Family/Friends, Trouble) Interactive System (CRAFFT-IS) to increase the frequency and quality of screenings in pediatric primary care, support a personalized response to results, and efficiently address alcohol and drug use and associated riding risks [22]. The CRAFFT-IS comprises a computer self-administered screening for patients (using the well-validated and widely used CRAFFT screening tool [23-25]), followed by psychoeducational content on the health risks of substance use, which adolescents complete before the clinician encounter. Clinicians access a computerized dashboard to view their patient’s screening results and prompts for brief motivational interviewing (MI)–based counseling tailored to their patient’s screening responses (clinician report).

CRAFFT-IS development was informed by the information-motivation-behavioral skills model [26], the health belief model [27,28], and social cognitive theory [29,30]. These models posit that individuals’ health risk behaviors are predicted by their *attention* to the behavior, *knowledge* about its health impacts, perceived *severity* of the harms that could result, perceived *benefits* of avoiding the behavior, and perceived *self-efficacy* to avoid the behavior. The CRAFFT-IS uses an MI-based approach to alert patients’ attention to the topic of alcohol use within a health context, enhance their awareness and perceived severity of the potential health harms of alcohol use, and boost their motivation and self-efficacy to avoid use.

We tested an initial version of the CRAFFT-IS among adolescent primary care patients at 9 practices in 3 New England states (Connecticut, Massachusetts, and Vermont) using a quasi-experimental design in which each office served as its own historical control (usual care [UC] phase followed by intervention phase; details reported elsewhere) [31-34]. Compared to UC patients, intervention patients reported double the rate of receiving clinician advice about alcohol and, among those with prior drinking at baseline, had one-third lower drinking risk in the 3-month follow-up [31]. We also found a 22% lower risk for heavy episodic drinking (HED) among those with prior HED at baseline and a 30% lower risk for riding with a driver who is substance impaired [33].

We then enhanced the clinician advice to include brief MI strategies (eg, eliciting a patient’s own reasons for avoiding use) while keeping the counseling brief enough for delivery by busy primary care clinicians. We pilot-tested this enhanced system compared to UC among adolescent patients seen for well visits at 5 Boston-area pediatric practices in a patient-randomized controlled trial. Intervention patients reported a 21% higher rate of receiving counseling about alcohol. Those reporting prior drinking at baseline (n=192) had a 34% lower risk for reporting HED during the 12-month follow-up [22]. Furthermore, those with riding risk at baseline (n=99) had a 42% lower risk of reporting riding with a driver who is substance impaired at the 12-month follow-up [35]. The CRAFFT-IS was also highly acceptable to the clinicians in the study, with 90% of the 49 clinicians agreeing that the system was useful, and 82% reporting that it increased their confidence in providing brief counseling [36].

To evaluate the replicability of these findings in a larger, more geographically diverse sample, we are now conducting a multisite effectiveness trial of the CRAFFT-IS among adolescent patients aged 14 to 17 years presenting for a well visit at practices within the national AAP Pediatric Research in Office Settings (PROS) network. This trial uses a clinician-randomized design, plans an adequately powered sample, and tests the intervention more broadly beyond New England. The CRAFFT-IS being tested in this study includes an updated version of the CRAFFT screen that includes nicotine vaping, now a leading form of substance use among adolescents [37]. It also includes updated psychoeducation material to reflect more current scientific knowledge and a revised brief counseling protocol to enhance alignment with MI-based counseling approaches.

### Objectives

The primary objective of the Adolescent Substance Use Prevention and Intervention Research (ASPIRE) study is to test the effect of the CRAFFT-IS on past 90-day HED over 12 months’ follow-up among adolescents who report past 12-month drinking at baseline. Our secondary objective is to test the effect of the CRAFFT-IS on riding with a driver who is substance impaired or driving while substance impaired (*riding or driving risk*) over 12 months’ follow-up. Additional exploratory study objectives include evaluating (1) hypothesized effect mediators (eg, perceived risk of harm and refusal self-efficacy) and moderators (eg, baseline risk level and gender), (2) efficacy for reducing the use of other commonly used substances among adolescents (ie, nicotine and cannabis), and (3) efficacy for reducing the negative consequences of substance use.

## Methods

### Study Team

This study is being performed in the national AAP PROS network of pediatric primary care practices.The AAP PROS network consists of pediatrician members whose guiding mission is to improve the health of children and enhance primary care practice by conducting and fostering national collaborative practice-based research. Boston Children’s Hospital (BCH) investigators are conducting the study in collaboration with the AAP PROS team. BCH conducts patient recruitment; participant retention; and data collection, management, and analysis activities. BCH also provides training and fidelity monitoring for clinicians delivering the intervention and convenes the data safety and monitoring board (DSMB). The AAP PROS team leads practice and clinician recruitment and data collection activities and hosts 2 PROS-member pediatrician advisors who provide input on study decisions from the perspective of community-based pediatric primary care clinicians.

### Ethical Considerations

The AAP Institutional Review Board (IRB) is the single IRB for the study. The AAP IRB initially approved this study on May 27, 2022, after full board review (#22 HA 01). Approval included a waiver of parental permission and a partial waiver of Health Insurance Portability and Accountability Act (HIPAA) authorization. We sought a partial waiver of HIPAA authorization because patient recruitment activities involve the exchange of patient health information from practices to the BCH study team. Furthermore, we sought a waiver of parental permission due to the minimal risk nature of the study, the developmental maturity of the target sample (adolescents aged 14-17 years), and the sensitivity of the substance-related topic. Our previous study on consent in adolescent substance use research showed that requiring parental permission resulted in a substantially higher study refusal rate (60% vs 20%) and a sample biased toward lower levels of substance use and substance-related problems [38]. Importantly, recruitment and assent materials state the voluntary nature of the study, emphasize that eligible adolescents *do not* have to have used alcohol or other substances to join the study, and encourage—but do not require—adolescents to discuss the study with their caregivers. The combination of these conditions supports parental involvement, preserves the privacy and confidentiality of adolescents who *do* use alcohol or other substances, and acknowledges adolescent autonomy to make an informed decision about participating.

The protocol version described in this paper was approved on June 21, 2023. Should there be modifications to the approved protocol or study materials, we will submit an amendment to the AAP IRB, and if applicable, the relying IRB at BCH. In addition, we will report scientific changes to the National Institute on Alcohol Abuse and Alcoholism (NIAAA) as needed or in the yearly progress report, at which point we will also update the trial registry on ClinicalTrials.gov.

In this trial, patient privacy and confidentiality protection is supported by executing a data transfer agreement between participating practices and BCH, assigning patients a numeric study identifier and by storing identifiable data in secure and restricted-access network locations separate from survey data. This study operates under a National Institutes of Health certificate of confidentiality. Assent materials state that only deidentified data will be shared outside of the study team (refer to the Data Access and Dissemination subsection).

Participating clinicians and practice staff members are required to provide informed consent. AAP PROS staff will send study recruitment materials to the designated contact clinician at each potentially eligible practice. Practices that are interested in participating will have a designated lead clinician submit a practice intake survey to confirm study eligibility of the practice and its clinicians. If practices are eligible, the AAP PROS staff will obtain written informed consent from all participating clinicians (Multimedia Appendix 1) as well as designated practice staff members who will handle and exchange patient data, answer patient or family questions, and otherwise support study activities at their site. Each participating practice will be offered a US $1000 honorarium after concluding patient recruitment at their practice and be able to keep all intervention-related materials, including the tablet computers provided for CRAFFT-IS implementation. Clinicians will be offered lunch accommodations (up to US $25 per person) for attending study orientation training and debriefing focus groups. In addition, clinicians in both trial arms can receive up to 12 continuing medical education credits for completing study training activities (UC clinicians will be offered CRAFFT-IS training at study completion at their practice). Board-certified pediatricians in the intervention arm may also receive optional maintenance of Certification Part 4 (up to 25 points) for a quality improvement activity spanning at least 3 quarterly feedback cycles. To complete this certification, intervention clinicians receive their participating patients’ aggregated postvisit data reporting receipt of counseling and compare their performance with a standardized benchmark. Intervention clinicians receive a US $5 electronic merchandise gift card for attending an optional *office hour* with the trainers by videoconference every 1 to 2 months and US $10 for completing a debriefing survey about their experience of, and views about, the CRAFFT-IS at study completion.

Adolescents must provide verbal informed assent to participate (Multimedia Appendix 2). On a regular schedule (eg, every 2 weeks), each practice will send a BCH research assistant (RA) a list of age-eligible adolescent patients with upcoming well visits in the next 2 to 6 weeks. The BCH RA will then mail a study invitation coaddressed to adolescents and their caregivers, which includes an informational letter on the practice’s letterhead and a study flyer with a QR code that leads to the brief study eligibility survey. Recruitment materials emphasize that adolescents do not need to have used substances to join the study, just as those with riding risk do not need to have used a substance themselves. Within 2 weeks of an adolescent’s scheduled visit, the RA will attempt to contact the adolescent by telephone to invite them to complete the eligibility survey, which the RA, based on the adolescent’s preference, can administer verbally or send for self-completion using an electronic link by SMS text message or email. At any point, a caregiver or adolescent can opt out of being contacted further. Eligible patients will be directed to an electronic information sheet and a 5-minute video brochure developed in collaboration with youth advisors. During a telephone call before the adolescent patients’ visit, a BCH RA will summarize key information using a standard assent script. If willing to join the study and able to answer 6 questions assessing study understanding correctly, adolescents will have the option to discuss the study with a parent or guardian and may then provide their verbal assent to participate. Adolescents who turn 18 during the study period will be asked to consent as an adult on or near their 18th birthday.

In addition to obtaining study assent, we will ask adolescents whether they assent or decline to have their deidentified study data shared with the NIAAA Data Archive (NIAAA_DA_), a national data repository to which NIAAA-funded investigators conducting human subjects research are expected to submit deidentified individual-level data [39]. This data sharing is not a condition of study participation and does not require parental permission. Adolescents can receive up to US $100 in small-value merchandise electronic gift cards for completion of study surveys (US $5, US $10, or US $15 for a survey, depending on its length).

### Study Design and Randomization

The study is a cluster randomized controlled trial involving 2 arms, intervention (CRAFFT-IS) and control (UC), with prospective follow-up for 12 months. Clinician randomization occurs within practice and on a rolling basis as practices enroll into the study. Participating pediatric primary care clinicians (doctor of medicine [MD], doctor of osteopathic medicine [DO], nurse practitioner [NP], and physician assistant [PA]) are randomly assigned to 1 of the study arms in a 1:1 ratio. Randomization is performed using a computerized, adaptive biased coin minimization scheme, which minimizes imbalance on the following factors, ranked by priority: clinician type (MD or DO vs NP or PA) and years in practice (≥10 vs <10) [40,41]. Compared to permuted blocks, adaptive biased coin minimization randomization has superior efficiency for achieving balance across multiple factors in studies with small units of randomization.

Clinicians are assigned a unique numeric code for temporary blinding while being randomized. After randomization, clinician study arm assignments are unblinded and shared with the study team. Study arm assignments cannot be blinded because the study team needs to train clinicians according to group assignment.

### Study Population, Sample Size, and Statistical Power

#### Practices and Clinicians

We will recruit up to 20 practices within the AAP PROS network, with up to 40 clinicians enrolled across these practices. To be eligible to participate, practices must (1) have at least 2 interested and eligible clinicians (clinician eligibility criteria are presented later in this subsection), (2) have a high-speed wireless internet connection available to ensure connectivity of study tablet computers, and (3) have an adolescent patient population that is primarily English speaking (the CRAFFT-IS has, to date, been tested only in English). Practices must not (1) be a practice or continuity clinic where residents or medical students routinely provide adolescent care (because trainees may not be available for training, implementation, and data collection for the duration of the practice’s participation in the study) or (2) have recently participated or be participating in other initiatives to improve adolescent substance use screening and brief intervention in their practice. Eligible clinicians (1) must be a clinician (MD, DO, NP, or PA) who sees patients for well visits and (2) must see ≥6 adolescents aged 14 to 17 years per week, on average, or approximately 300 adolescents per year, for well visits.

#### Adolescents

We aim to enroll a minimum of 1300 adolescent participants. Eligible adolescents must (1) present for an annual well visit with a participating clinician in either study arm, (2) be aged 14 to 17 years at the time of their well visit, (3) report past 12-month alcohol use or past 12-month riding risk, and (4) have a smartphone and be willing to share their mobile phone number with the study team. We chose the minimum age of 14 years because there is low prevalence of prior alcohol use among younger adolescents (<5% of adolescents aged 12-13 years in our prior studies reported past 12-month drinking [[name], unpublished data, 2019]). In addition, to be considered fully enrolled, all adolescents must complete the previsit survey before seeing their clinician, as well as the CRAFFT screen for those scheduled to see a clinician in the intervention arm. Adolescents must be willing and able to complete monthly surveys for 12 months after their well visit.

Adolescent patients must not be (1) in foster care, (2) in college or trade school at the time of their well visit, (3) currently receiving counseling or treatment for a substance use concern from a specialty clinician, or (4) perceived by their clinician to be inappropriate for the study (eg, due to neurodevelopmental delays or another medical priority at the time of visit).

We calculated the adolescent patient sample size by applying recruitment and retention rates, alcohol use and riding risk prevalence rates, intervention effect sizes, a within-clinician clustering design effect (0.90), and the clinician intraclass correlation coefficient for HED (0.008) seen in our pilot study [22]. We estimated a 37% past 12-month drinking prevalence rate, 28% riding risk prevalence rate among adolescents with past 12-month drinking, and a 5.8% riding risk rate among those with no past 12-month drinking. The 37% past 12-month drinking prevalence rate is similar to the 36.1% prevalence rate found on the 2018 Monitoring the Future Survey [42]. We applied slightly more conservative rates of participation (80% vs 82%) and retention (70% vs 75%) than those found in our pilot study to ensure that we achieve a sample size with sufficient power. With α set at ≤.05 and β at ≥.80, our power calculation indicated that a minimum analysis sample size of 888 participants with 12-month follow-up data would provide 86% power to detect an effect size of ≥20% in our primary outcome measure of HED. Applying the conservative estimate of 70% retention at 12 months, we need to recruit a minimum of 1268 participants. Thus, we estimate needing approximately 4200 adolescents to complete the eligibility survey, with 1600 (40% of those screened) meeting eligibility criteria, and 1300 (80% of those eligible) enrolling. To enroll this sample, we anticipate enrolling an average of 40 patients per clinician among up to 40 clinicians completing the study.

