### Intervention

#### Overview

The CRAFFT-IS was developed to leverage the power of digital technology to provide a time-efficient and feasible way for busy pediatric practices to improve both the frequency and quality of adolescent substance use screening and counseling in primary care. To this end, the CRAFFT-IS consists of the following components: (1) previsit self-administered screen (CRAFFT version with extra questions that are related to nicotine vaping and tobacco use [CRAFFT 2.1+N]), immediately followed by (2) brief interactive psychoeducational content on substance use–related health risks, and (3) clinician delivery of brief MI-based counseling during the confidential portion of the well visit, guided by a computerized point-of-care decision support tool called the clinician report. In addition, as an intervention to reduce riding and driving risk, intervention clinicians provide all participating patients and their caregivers with the *Contract for Life* document [34,43]. These components are described in greater detail in the following subsections.

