##### Adolescents

All adolescent participants are assigned a unique numeric identifier at the time of recruitment for use in data collection, storage, and linkage throughout their study participation. Once assented, participants indicate their contact preferences. Adolescents who agree to have their data shared with the NIAAA_DA_ are assigned a Global Unique Identifier using their first, middle, and last names; sex assigned at birth; and date and city of birth. Global Unique Identifiers are numeric codes that allow participant data to be submitted to the NIAAA_DA_ without any personally identifiable information. All participants self-administer the confidential electronic previsit survey (approximately 20 min; refer to Table 2 for details on all surveys), and participants seeing an intervention clinician complete the screening and psychoeducational components of the CRAFFT-IS (5 min) before seeing their clinician. After their visit, all participants complete the immediate postvisit survey (approximately 10 min), and then, through the 12-month follow-up period, brief monthly surveys about their past 30-day substance use and longer surveys at 3, 6, 9, and 12 months (approximately 15 min each). Participants may choose to skip questions or entire surveys and still remain in the study.

All surveys can be completed electronically on smartphones and desktop or tablet computers through a link sent by SMS text message or email to participants’ personal mobile phone numbers or email addresses, as preferred. Electronic surveys are protected by a password set by the adolescent. Adolescents can also complete a survey by mobile phone with a study RA. If the adolescent does not complete a survey after electronic reminders, a study RA will call the adolescent to encourage survey completion.

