#### Data Analysis Plan

Analysts will be blinded to treatment arm. We will evaluate randomization success and level of attrition bias by comparing baseline characteristics of adolescents by treatment arm and by those retained versus those lost to follow-up (ie, adolescent participants who stop completing study surveys during the 12 months after their well visit). Baseline variables meeting a *P* value of <.20 in randomized group comparisons will be entered as control variables in multivariable modeling of the intervention effect to yield adjusted estimates of effect. We will compare rates of counseling receipt and patient ratings of their visit between groups. We will also generate variables related to intervention *dose* (eg, receipt of clinician counseling and receipt of *Contract for Life*) for use in sensitivity analyses.

To assess intervention effects on our primary and secondary outcome measures (past 90-day HED and any past 90-day riding or driving risk) at each of the 3-, 6-, 9-, and 12-month follow-up time points, we will use multiple logistic regression modeling with generalized estimating equations to compute adjusted relative risk ratios (CRAFFT-IS vs UC). Generalized estimating equations account for clustering of participants within practice and clinician. Furthermore, we will explore intervention effects on the number of days of drinking and of HED and on the number of times participants experienced alcohol-related negative consequences from baseline to each follow-up time point. As these variables are likely to have distributions that are highly skewed and overdispersed, we will specify a negative binomial distribution and log link in these regression models. We will also conduct longitudinal data analysis using mixed effects modeling to compare group outcomes trajectories through the entire 12-month follow-up period. We plan to explore intervention effect mediation by applying the product of coefficients test for mediation [71,72] and potential effect moderation by future-determined variables by testing the significance of interaction terms in regression models.

All intervention effect analyses will use intent-to-treat groups. We will transform continuous variables with skewed data and collapse categories as needed to preserve adequate cell sizes. To handle missing data, we will use multiple imputation based on regression modeling and compare the results of analyses using the imputed data set versus the original data set [73].

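### Full enrolment requires completing the CRAFFT screen, itself part of the intervention, in the intervention arm only; on its plain reading this conflicts with intent-to-treat and can bias the comparison, by an unknown amount and in an unknown direction

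*Protocol article*

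**What the plan says.** - **Timing of allocation** (Study Design and Randomization): "Clinician randomization occurs within practice and on a rolling basis as practices enroll into the study". Then: "After randomization, clinician study arm assignments are unblinded and shared with the study team". According to the Study Team section, the Boston team also recruits the adolescents, so it knows the arm when it does so.
- **Enrolment rule** (Study Population, Sample Size, and Statistical Power, subsection Adolescents): "to be considered fully enrolled, all adolescents must complete the previsit survey before seeing their clinician", and the sentence continues "as well as the CRAFFT screen for those scheduled to see a clinician in the intervention arm". No matching extra task is set for usual care.
- **Nature of the screen** (Intervention, Overview): "CRAFFT-IS consists of the following components: (1) previsit self-administered screen". Footnote a of Table 2 confirms that it is collected in the intervention arm only. Data Collection, subsection Adolescents, adds: "participants seeing an intervention clinician complete the screening and psychoeducational components of the CRAFFT-IS (5 min) before seeing their clinician".
- **Analysis principle** (Data Analysis Plan): "All intervention effect analyses will use intent-to-treat groups".
- **Nearby rules**: Intervention Modification or Discontinuation keeps the data of withdrawn participants. Data Collection lets participants skip whole surveys without leaving the study. The Data Analysis Plan treats receipt of counseling and of the Contract for Life as dose variables for sensitivity analyses. None of these says what happens to an adolescent who completes the survey but not the screen.

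**The concern.** Take two identical adolescents who assent, complete the previsit survey and attend the visit without doing the screen. The one seeing a usual-care clinician is fully enrolled. The one seeing an intervention clinician is not. The only difference is the clinician's arm, and the missing step is part of the treatment under test. Adherence to the first component thus becomes an entry condition in one arm, applied after allocation.

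If full enrolment decides who is followed and analysed, the arms are selected differently, and an intent-to-treat label on those who remain does not undo that. The article's other safeguards do not reach these adolescents. The withdrawal rule presupposes that they were enrolled. The attrition comparison covers those retained against those lost to follow-up. Multiple imputation fills gaps only for people in the data set. At stake is the primary comparison of HED and, in the same way, the riding and driving outcome.

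**Working it through.** **The plan's own figure.** 888 / 0.70 = 1268.6, which agrees with the stated 1268. The enrolment rule does not affect this number. The stated 86% power cannot be checked, because no usual-care HED risk is given.

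**Inputs from the article.** 888 analysed participants, allocated 1:1 at clinician level, so about 444 per arm; design effect size 20%; clinician intraclass correlation 0.008; up to 40 clinicians.

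**Inputs not in the article, so assumed.** f = share of intervention-arm adolescents who complete the survey but not the screen; k = their HED risk divided by that of completers; p = usual-care HED risk.

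**Risk ratio with no true effect.** Let r be the risk among would-be completers. Usual care keeps everyone, so its risk is p = (1 - f)r + f*k*r. The intervention arm keeps completers only, so its risk is r. Hence

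RR = r / p = 1 / (1 - f + f*k).

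The last column is a two-sided 5% test with 444 per arm and p = 30%, ignoring clustering and adjustment: z = (p - r) / sqrt[p(1 - p)/444 + r(1 - r)/444], rejection = 1 - Φ(1.96 - z) + Φ(-1.96 - z).

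| f | k | 1 - f + f*k | RR | (1 - RR)/0.20 | Rejection at p = 30% |
|---|---|---|---|---|---|
| 2% | 1.25 | 1.005 | 0.995 | 2% | 5.0% |
| 5% | 1.5 | 1.025 | 0.976 | 12% | 5.7% |
| 10% | 1.5 | 1.05 | 0.952 | 24% | 7.5% |
| 10% | 2 | 1.10 | 0.909 | 45% | 14.7% |
| 15% | 2 | 1.15 | 0.870 | 65% | 25.5% |

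**Other direction.** For f = 10%, k = 0.67: 1 / (0.90 + 0.067) = 1.03, so the bias runs against the intervention.

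**Sensitivity to p.** For f = 10%, k = 2, rejection is 10.6% at p = 20% and 20.0% at p = 40%.

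**Clustering.** 888 / 40 = 22.2 analysed per clinician; design effect 1 + 21.2 × 0.008 = 1.17. For f = 10%, k = 2, p = 30%, z falls from 0.90 to 0.90 / sqrt(1.17) = 0.83, and rejection from 14.7% to about 13%.

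**With one definition for both arms.** Both arms then keep completers and non-completers, so with no true effect RR = 1 for any f and k.

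**The case against.** Four arguments tell against a stronger reading.

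1. *Exclusion from analysis is not stated.* A reader might infer that the article says non-completers are removed from the analysis. It says only who counts as fully enrolled, and the analysis set may be defined in a fuller document that is not shown. This stands as a limit on certainty. Exclusion is still the plain meaning of an enrolment condition, and nothing in the article says these adolescents are kept.

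2. *Direction is not known.* A reader might infer that non-completers drink more, so that the bias favours the intervention. The article does not say so. By this step both arms have answered CRAFFT items in the eligibility survey and a previsit survey of about 20 minutes with detailed drinking questions. Adolescents reluctant to disclose may already have left, in both arms alike. Missing the screen could simply reflect late arrival. This stands.

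3. *The loss may be trivial.* Screen and psychoeducation together take about 5 minutes, and the screen can be done on a smartphone or on a tablet at the visit. This stands: for small f the bias is negligible.

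4. *The planned model adjusts.* Baseline variables that differ between arms at P<.20 enter as covariates, and baseline drinking is measured in both arms. Selection acting through measured drinking would therefore be partly detected and adjusted. This stands in part. It does not deal with unmeasured differences, and it cannot return people who are outside the data set. It does mean that the rejection rates above, from an unadjusted and unclustered test, are illustrations and not the error rate of the planned analysis.

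There is also an operational reason for the rule: the clinician report draws on the screen responses. That bears on whether the intervention can be delivered in full, not on who should be analysed.

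**Conclusion.** The point holds in this form: the article sets an enrolment condition that differs by arm, comes after clinician randomization and consists of completing part of the intervention. As written, it permits arm-dependent selection and conflicts with the intent-to-treat statement.

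The size and direction of any bias are unknown. Over the values of f and k shown, with k above 1, the risk ratio with no true effect runs from 0.995 to 0.87, which is about 2% to 65% of the 20% effect the trial is designed to detect. With k below 1 it exceeds 1. These figures rest wholly on assumed f and k, and on non-completers being neither followed nor analysed. The documents do not support a claim that the result will favour the intervention, or that the type I error is inflated to any particular level.

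**What to change.** - Define full enrolment identically in both arms: assent plus the previsit survey completed before seeing the clinician. Delete the CRAFFT-screen clause.
- State that intervention-arm adolescents who do not complete the screen are followed and analysed in their clinician's arm. If this is already the practice, saying so settles the matter.
- Treat screen completion as an intervention-dose variable, alongside receipt of counseling and of the Contract for Life.
- For adolescents already set aside for this reason, report their number and available baseline data by arm, and resume follow-up only where assent and timing permit. Past 90-day outcomes for windows that have elapsed cannot be recovered from a previsit survey, so restoring these adolescents in full may not be possible.

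The cost is a short amendment, slight dilution of the effect, and follow-up of some additional intervention-arm adolescents. With about 634 per arm (1268 / 2), f of 2% to 15% would mean roughly 13 to 95 of them. The recruitment target does not change.
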